#### App Use

The open-source web analytic platform Matomo Analytics [43] will be used to investigate user statistics and traffic in the app. In-app user analytics will be collected to track user behavior such as the number of app sessions, length of app sessions, frequency of use, date the app was first opened, the number of pages, time spent on the pages, and bounce rate.

#### Health-Related Outcomes

Health-related outcomes will be collected at baseline upon registration for the pilot version of the Bone@BC app and then at 3 different time points (Table 2).

**Table 2 table2:** Study assessments and time points stage 4.

Data Collection (n=50)			Baseline		Week																					
					1		2	3		4 (~1 mo)		5		6		7		8 (~2 mo)		9		10		11		12 (~3 mo)
**Data for the research database REDCap^a^**																										
	Informed consent	✓																								
	Demographic data^b^	✓																								
	EORTC QLQ-C30^c^	✓							✓																✓	
	SES6G^d^	✓							✓								✓								✓	
	heiQ^e^	✓																							✓	
	HADS^f^	✓																							✓	
	SGPALS^g^	✓							✓								✓								✓	
	SUS-DK^h^																								✓	
	Open-source web analytic platform Matomo Analytics 3.0^i^	✓							✓								✓								✓	
**PRO^j^ data through the app**																										
	Electronic patient-reported PRO questionnaires on symptoms Bone@BC (everyday)^k^	✓		✓		✓		✓	✓		✓		✓		✓		✓		✓		✓		✓		✓	
Semistructured interviews																										✓

^a^REDCap: Research Electronic Data Capture.

^b^Demographic data (eg, marital status, family status, educational level, and occupation).

^c^EORTC QLQ-C30: European Organization for Research and Treatment of Cancer Quality of Life C30.

^d^SES6G: Self-Efficacy for Managing Chronic Disease 6-Item Scale.

^e^heiQ: Health Education Impact Questionnaire.

^f^HADS: Hospital Anxiety and Depression Scale.

^g^SGPALS: Saltin-Grimby Physical Activity Level Scale.

^h^SUS-DK: System Usability Scale–Danish version.

^i^Open-source web analytic platform Matomo Analytics.

^j^PRO: patient-reported outcome.

^k^Patient-reported outcomes from the app on the questions provided daily on health-related quality of life, late side-effects, symptoms and concerns perspectives, and level of physical activity in the Bone@BC app and question prompt list. Items developed in stage 3 and implemented from the European Organization for Research and Treatment of Quality of Life Item Library in the domains of late side-effects and symptoms management.

The health-related ePROs being assessed before and after the study will be the HRQoL by the 30-item EORTC Quality of Life C30 (QLQ-C30) [44]. The HRQoL domains are divided into multi-item subscales: functional (physical, role, cognitive, emotional, and social), symptom (fatigue, pain, nausea/vomiting, and dyspnea), financial adversity, and global health status [44]. The EORTC-QLQ-C30 has proven to be reliable and valid in a range of patient populations and a variety of treatment settings [52].

Self-efficacy will be measured by the Self-Efficacy for Managing Chronic Disease 6-Item Scale (SES6G) [45]. SES6G is a self-administered questionnaire with 6 items on the patient’s perceived self-efficacy on a 10-point Likert scale ranging from “not at all confident” to “totally confident” [45]. Ritter and Lorig [53] conducted 2 new studies and reviewed 8 independent studies to investigate the psychometric properties of the scale. Cronbach α was a minimum of .88 across all studies; minimal floor and ceiling effects were observed; the measure was sensitive to change; and moderate and significant correlations provide convergent validity evidence when measured against selected health indicators [53].

Physical activity will be measured by the Saltin-Grimby Physical Activity Level Scale (SGPALS) [46]. SGPALS is a 4-level scale. The questionnaire measures the level of physical activity as 3 months before the patients were diagnosed with BC and how the level of physical activity is today [46]. The SGPALS is found to be reliable, with a high level of validity and consistency [54].

Anxiety and depressive symptoms will be measured by the Hospital Anxiety and Depression Scale (HADS) [47]. HADS is a validated screening tool and includes 14 questions addressing anxiety and depressive symptoms with 7 items each in the previous 7 days [47]. In an updated literature review, the HADS was found to be reliable with a Cronbach α between .70 and .90 [55].

Patient empowerment will be measured by the Health Education Impact Questionnaire (heiQ) [48]. heiQ is an outcome and evaluation measure for patient education and self-management interventions for people with chronic conditions. heiQ is a validated screening tool and includes 42 questions with the following 4 options for the answer: “strongly disagree,” “disagree, agree,” or “completely agree” [48]. The heiQ is a valid, reliable measure of key dimensions of generic health-related empowerment [56].

### Statistical Analysis

#### Preestablished Criteria

Feasibility will be explored by looking at the success threshold, attrition rate, and adherence. The success threshold of ≥60% will be defined as the proportion of informed patients giving consent. The attrition rate will be calculated as the proportion of participants withdrawing from the intervention, leaving no data on outcomes available. The retention rate of ≥85% will be the number of individuals who remained in the study and responded to the daily PRO in 12 weeks. The retention rate and success threshold are based on a recent systematic review of internet-based supportive care for patients with lung disease [57]. Patient adherence will be the proportion of patients completing self-reports for each time point adjusted for withdrawals. The adherence rate is the proportion of patients replying to ≥80% of the daily PRO questions. Adherence to daily completion will be analyzed according to, for example, material status and educational level using the Fisher exact test.

Acceptability will be assessed based on the following predetermined criteria: (1) system usability score ≥68% [42]; (2) patients’ experience identified in follow-up interviews; and (3) HRQoL must be at least at the same level before and after the intervention as measured by the EORTC QLQ-C30 [44].

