#### Stage 3: Multimethod Exploratory Study

In this stage, an electronic Patient Concerns Inventory list (PCI) will be adapted from the English version of the PCI developed by Kanatas et al [40] for patients with BC. The adapted PCI will be modified to fit the app. A PCI is a structured list of frequently asked questions and concerns. It is designed to support and encourage patients to acquire information during their communication with HCPs. The development of the electronic PCI relies on the following steps: (1) translation and linguistic validation according to the Professional Society for Health Economics and Outcomes Research [41]; (2) focus group interview with the patient advisory board; (3) development of a minimum variable product (MVP) app only to test the electronic PCI list; (4) the patient advisory board testing the MVP app and evaluating it in a focus group interview; (5) pilot-test patients (n=15) using the MVP app will be interviewed by semistructured face-to-face interviews; and (6) harmonization meeting in the multidisciplinary research team.

The identified items from the EORTC Library [39] and the PCI will be implemented in the pilot version of the Bone@BC app.

#### Stage 4

Stage 4 is a convergent, nonrandomized, single-arm mixed methods feasibility study [21] (Figure 4 [20,21,42-49]) investigating the feasibility of the pilot version of the Bone@BC app.

The purpose of this stage will be to explore the patients’ perspectives on feasibility, acceptability, and usability while being offered the pilot version of the Bone@BC app, which will be provided to them as a tool for symptom identification over a period of 12 weeks. Moreover, the consent rate, attrition rate, adherence rate, and retention rate will be explored. Furthermore, the potential changes in self-efficacy, HRQoL, and patient empowerment over time will be measured. The findings from the quantitative data (PRO questionnaires and data in the Bone@BC app) and the qualitative data (patient interviews) will be compared and merged. The intent is to obtain a more comprehensive understanding of the feasibility, usability, barriers, and subgroup of patients who may benefit from using the app.

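### Acceptability criterion (3) is a pass/fail rule on quality of life with an implied zero margin, no named QLQ-C30 scale and no decision statistic, so the same data could be declared a pass or a fail

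*Protocol article*

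**What the plan says.** The Preestablished Criteria section introduces three conditions with "Acceptability will be assessed based on the following predetermined criteria". The first is a usability score threshold, the second is patients' experience from interviews, and the third is "HRQoL must be at least at the same level before and after the intervention as measured by the EORTC QLQ-C30".

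The Health-Related Outcomes section describes the instrument as having "multi-item subscales: functional (physical, role, cognitive, emotional, and social), symptom (fatigue, pain, nausea/vomiting, and dyspnea), financial adversity, and global health status". That is 5 functional, 4 symptom, 1 financial and 1 global domain, 11 in all. None is designated for the criterion.

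The Quantitative Data section says that the analysis in general will rest on confidence intervals, and that continuous variables may be summarised by mean or median depending on normality. It does not link either statement to criterion (3). Stage 4 is a "convergent, nonrandomized, single-arm mixed methods feasibility study". The Power section plans 40 to 50 participants without a formal calculation.

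**The concern.** Consent, retention, adherence and usability each have a numeric threshold in the same section. The quality-of-life rule is worded just as firmly, but "at least at the same level before and after the intervention" leaves no room for sampling error and does not define what is compared. The Abstract places acceptability within the primary outcome, so this is not a side measure.

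If the rule stays as it is, the choice of scale and statistic falls to whoever analyses the data after seeing them, and that choice can decide the result. With one arm, any general change in quality of life over 12 weeks enters the result as if the app had caused it.

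**Working it through.** The plan states no error rate or power for this criterion, so there is no figure of its own to reproduce. The check is how often an app with no effect would fail under each reading that the wording permits.

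**Inputs from the protocol:** n = 40 to 50 (Power); retention target 85%, so at the threshold 0.85 × 40 = 34 women from the smaller sample; 11 listed domains; one arm; 12 weeks.

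**Assumptions, not in the protocol:** SD of individual change 15 to 25 points on a 0 to 100 scale; normal approximation for the mean change; for the median reading, a global score that moves in steps of 8.33 points.

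**Standard error:** SE = SD/√n, from 15/√50 = 2.12 to 25/√40 = 3.95.

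**Step 1. Failure with a true change of zero**

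| Reading of the rule | Formula | Fails |
|---|---|---|
| Mean change ≥ 0, one scale | Φ(0) | 50% at any n and SD (48% to 49% allowing for exact ties) |
| Mean change ≥ 0 on both of two scales, correlation 0.3 to 0.7 | simulation | 63% to 70% |
| Lower 95% limit ≥ 0, one scale | 1 − Φ(−1.96) | 97.5% |
| Not significantly worse (95% CI not wholly below 0), one scale | Φ(−1.96) | 2.5% |
| Median change ≥ 0, one scale | simulation | about 7% to 25% |

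**Step 2. One data set, opposite results.** Take n = 45, SD = 20 and a hypothetical observed mean change of -2. Then SE = 20/√45 = 2.98, and the 95% interval is -2 ± 1.96 × 2.98, or -7.8 to 3.8. The mean-change reading fails, the lower-limit reading fails, and the not-significantly-worse reading passes.

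**Step 3. Background drift.** If the app does nothing but quality of life drifts by d points, the mean-change rule fails with probability Φ(−d/SE). For an assumed d = +2, this is Φ(−2/2.12) = 17% to Φ(−2/3.95) = 31%. For d = -2, it is 69% to 83%.

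**Step 4. The lenient reading.** With a true 5-point fall, not significantly worse passes with probability Φ(1.96 − 5/SE). This is 35% (SD 15, n = 50) to 76% (SD 25, n = 40).

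**Step 5. Rules with a tolerance m, one scale, true change zero.** For a point-estimate rule, P(fail) = Φ(−m/SE). For a lower-limit rule, P(pass) = Φ(m/SE − 1.96).

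| Rule | n = 45, SD 20 | n = 40 to 50, SD 15 to 25 |
|---|---|---|
| Mean change above -5 | fails 4.7% | fails about 1% to 10% |
| Lower 95% limit above -10 | passes 92% | passes 72% to 99.7% |
| Lower 95% limit above -5 | passes 39% | passes 24% to 65% |

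With only 34 women retained, the three rows become: fails 3% to 12%, passes 65% to 97%, passes 21% to 49%.

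**The case against.** The strongest reply is that a scale and decision statistic are commonly left to an analysis plan, which is not shown here, and that a confidence-interval approach is already announced. On that approach the rule could mean not significantly worse, which fails only 2.5% of no-change studies. This stands in part: the 50% belongs to one reading and is not a property of the plan. It does not remove the problem. The protocol itself states the rule as preestablished, worded with a zero margin, and does not tie the interval approach to it. The lenient reading also passes a true 5-point fall often.

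It is also fair that nothing says all three acceptability conditions must be met, and that interviews carry much of the assessment. No stop or go decision hangs on criterion (3) alone.

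A reader might infer more than the protocol supports:

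- *That the criterion is almost certain to fail because every domain must hold.* With 11 domains and correlation 0.3 to 0.7, failure would be 83% to 97%. But the protocol says only that quality of life must hold; it nowhere requires all domains.
- *That the missing control causes the 50%.* It does not. The 50% comes from the zero margin. Lack of a control lets drift push the rate up or down.
- *That the QLQ-C30 schedule undermines the rule.* The text says "The health-related ePROs being assessed before and after the study will be the HRQoL by the 30-item EORTC Quality of Life C30" and elsewhere "and then at 3 different time points (Table 2", while Table 2 shows baseline, week 4 and week 12. This is loose wording. Table 2 contains the two assessments that a before-and-after rule needs, and the phrase about three time points covers the outcomes collectively.
- *That uncontrolled QLQ-C30 change will be used to identify a benefiting subgroup.* The phrase "barriers, and subgroup of patients who may benefit from using the app" describes the aim of merging quantitative and qualitative data. It does not say that change on this instrument will define the subgroup.

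**Conclusion.** The point holds as a badly fixed rule. On its plain reading (mean change of zero or more, one scale, no drift), an ineffective but harmless app fails about 50% of the time, and a larger sample does not help. Across the readings that the wording allows, failure under no change runs from 2.5% to 97.5%. The 50%, 2.5% and 97.5% need no assumed SD. The drift and tolerance figures rest on the assumed SD of 15 to 25 and on normality.

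The weakness lies in the criterion and its interpretation. It does not invalidate the other feasibility criteria, and on its own it does not decide whether the app is acceptable.

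**What to change.** Before stage 4 data are seen, rewrite criterion (3) so that it:

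- names one scale, for example global health status, and the comparison from baseline to week 12;
- replaces the requirement of an equal level with a tolerance that the sponsor justifies, and a decision statistic;
- states the chance of passing under no change, with the SD assumed.

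Two workable forms under the assumptions above are a mean change above -5, or a lower 95% limit above -10. A lower 95% limit above -5 is a poor choice here. It passes only 24% to 65% of no-change studies, so over much of that range it is worse than the present rule. The protocol gives no tolerance, so these values are illustrations.

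Report the mean change with its 95% interval whatever the result, report the other domains descriptively, and state that a single-arm change cannot be attributed to the app.

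The cost is a wording change, with no extra data collection. The downside is that a tolerance may let a small true fall pass. A mean-above-minus-5 rule passes a true 2-point fall with probability Φ(3/SE), or 78% to 92%, and a true 5-point fall half the time. A lower-limit-above-minus-10 rule passes a true 5-point fall with probability Φ(5/SE − 1.96), or 24% to 65%. The protocol should say so beside the rule it adopts.

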#### Quantitative Data

The quantitative data will be exported to R software (version 4.1.2; R Foundation for Statistical Computing) [58]. All questionnaires will be scored according to the specific manuals. The analysis of the obtained data will be based on CIs and will focus on exploring the longitudinal changes over time. The daily self-report of symptoms will be analyzed using multiple linear regression after the variables have been checked by diagnostic plots to see if they meet the following 5 main assumptions: (1) linearity, (2) homoskedasticity, (3) independence of errors, (4) normality, and (5) independence of independent variables. Descriptive statistics will be performed to describe the sociographic and clinical characteristics. The categorical variables will be reported as frequencies and percentages. Continuous variables will be tested for normality before we decide to report them as mean and SD or median and IQR. In addition, an open-source digital analysis platform (Matomo) [43] will be used to track traffic and user behavior on the app.

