**Objective:**

This study aims to (1) develop an electronic symptom management tool for patients with postmenopausal early breast cancer receiving maintenance aromatase inhibitors with an endocrine aspect and (2) assess the feasibility, acceptability, and usability of the pilot version of the Bone@BC app. Furthermore, longitudinally, symptom prevalence and quality of life for patients with postmenopausal nonmetastatic estrogen receptor–positive breast cancer will be explored.

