**Methods:**

This study follows a multistage research plan. In stage 1, a systematic literature review to establish an overview of aromatase inhibitor–related symptoms reported by postmenopausal women with nonmetastatic estrogen receptor–positive breast cancer will be completed. In stage 2, a comprehensive overview of symptoms related to aromatase inhibitors (letrozole, exemestane, and anastrozole) will be performed (eg, by reviewing medical leaflets and guidelines). In stage 3, an electronic app with a user-friendly Patient Concern Inventory list to comprise symptoms and concerns will be developed. Last, in stage 4, a convergent mixed methods feasibility study of the pilot version of the Bone@BC app will be conducted. A total of 45 patients with postmenopausal nonmetastatic estrogen receptor–positive breast cancer will use the app daily for symptom identification and respond to 6 serial patient-reported outcome measurements for 12 weeks. Finally, semistructured interviews will be performed. The primary outcome includes consent rate, attrition rate, retention rates, technical issues, and adherence, assessed using preestablished criteria on feasibility and a mixed methods approach for exploring acceptability. A patient advisory board consisting of 5 women with breast cancer is recruited to include their perspectives and experiences in the planning, organization, implementation, and dissemination of the research throughout the project.

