### Power

For the semistructured patient interviews, the sample size will be guided by the notion of information power, according to Malterud et al [50]. Being a feasibility study with predetermined criteria for success, a formal sample size calculation is not necessary [63]. However, sample sizes of 40-50 participants have been recommended for feasibility studies [64]. Thus, 40-50 participants will be recruited for the intervention.

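### Daily symptom reports, up to 84 per woman, are to be analysed by a linear regression that requires independent errors; taken record by record, its confidence intervals for the exploratory symptom results would be wrong

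*Protocol article*

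**What the plan says.** The Quantitative Data section of the protocol article names the model for the app data: "The daily self-report of symptoms will be analyzed using multiple linear regression after the variables have been checked by diagnostic plots". The assumptions to be checked are "(1) linearity, (2) homoskedasticity, (3) independence of errors, (4) normality, and (5) independence of independent variables". The same section sets the basis of inference: "The analysis of the obtained data will be based on CIs and will focus on exploring the longitudinal changes over time".

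The data structure is given elsewhere:

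- Table 2 lists "Electronic patient-reported PRO questionnaires on symptoms Bone@BC (everyday)" with a mark at baseline and in every week to week 12.
- The Stage 4 description offers the app to patients, "which will be provided to them as a tool for symptom identification over a period of 12 weeks".
- The Power section says: "Thus, 40-50 participants will be recruited for the intervention". The Abstract gives 45 and Table 2 gives n=50.

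No section mentions a random effect, GEE, clustered standard errors or per-woman summaries for the daily reports.

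**The concern.** Ordinary linear regression computes its standard errors as if every record were a separate piece of information. Daily reports from one woman are not. A woman with high symptom levels in week 1 tends to have high levels in week 8, and one bad day tends to follow another. The dependence is known before any data arrive, so a diagnostic plot can only confirm it.

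Because the section bases its inference on confidence intervals, wrong standard errors lead directly to wrong conclusions about how symptoms develop. Following symptoms over time is a stated further aim of the study, and this is the only model that the article names for the daily data.

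**Working it through.** **Inputs from the article.** Daily reporting for 12 weeks gives 12 × 7 = 84 reports per woman (85 if a separate baseline report is counted). For 40, 45 and 50 women that is 3,360, 3,780 and 4,200 records. The article has no formal power calculation, so there is no stated figure to reproduce.

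**Assumption.** The intraclass correlation (ICC) between reports from the same woman is not given. It is shown over a range.

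**1. Overall means and patient-level covariates.** The design effect is DE = 1 + (84 − 1) × ICC. The true standard error is √DE times the reported one. The real coverage of a nominal 95% interval is 2Φ(1.96/√DE) − 1.

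| ICC | DE | true SE / reported SE | coverage |
|---|---|---|---|
| 0.01 | 1.83 | 1.35 | 85% |
| 0.1 | 9.3 | 3.05 | 48% |
| 0.3 | 25.9 | 5.09 | 30% |
| 0.5 | 42.5 | 6.52 | 24% |

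At ICC 0.5, the 3,780 records from 45 women carry the information of 3,780 / 42.5 ≈ 89 independent ones for such quantities. If women answered on about 68 days (80% of 84, the adherence threshold applied to days), DE at ICC 0.5 is 1 + 67 × 0.5 = 34.5 and coverage is 26%.

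**2. Change over time.** If women differ only in level, the true standard error of the time slope is √(1 − ICC) times the reported one, because the regression counts differences between women as noise.

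- ICC 0.3: ratio 0.837, coverage 2Φ(1.96/0.837) − 1 ≈ 98%.
- ICC 0.5: ratio 0.707, coverage 2Φ(1.96/0.707) − 1 ≈ 99%.

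These intervals are too wide. The direction reverses once slopes vary or errors are autocorrelated.

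**3. Simulation.** Ordinary regression of the symptom score on day and a binary patient-level covariate, for 45 women with all 84 reports, 1,500 runs per setting. The slope SD is the between-woman SD of the 12-week change, in units of the SD of a single report.

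| ICC | slope SD | day-to-day autocorrelation | coverage, time | coverage, patient-level covariate |
|---|---|---|---|---|
| 0 | 0 | 0 | 95% | 95% |
| 0.3 | 0 | 0 | 98% | 31% |
| 0.5 | 0 | 0 | 99.5% | 23% |
| 0.5 | 0.5 | 0 | 80% | 24% |
| 0.5 | 1.0 | 0 | 54% | 26% |
| 0.5 | 0 | 0.5 | 89% | 22% |
| 0.3 | 0.5 | 0.5 | 67% | 28% |

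The simulation agrees with the formulas. With standard errors clustered by woman, coverage was about 94 to 96% for every coefficient in every setting.

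**The case against.** Several points on the other side stand.

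- **The analysis is exploratory.** A reader might infer that the feasibility verdict is at risk. It is not. Consent, retention, adherence, the usability score and the before-after QLQ-C30 comparison, all in Preestablished Criteria, do not use this regression.
- **The largest figures belong to quantities that the section does not name.** A reader might infer that spurious symptom predictors will be reported, since coverage of 24 to 48% means that a nominal 5% test of a null patient-level covariate rejects about half to three quarters of the time. But no covariates are listed for this model, and the sociodemographic comparison that is described concerns adherence and uses the Fisher exact test. For the stated focus, change over time, the direction of error is undetermined.
- **The unit of analysis is not stated.** One summary per woman would make independence reasonable. Nothing in the article points to such summaries, and regressing the daily reports themselves is the natural reading, but the criticism depends on that reading.
- **What follows a failed check may be in an analysis plan that is not shown.** The absence of a fallback is therefore not held against the article. The named method is, because the article itself fixes a model whose assumption its own design violates.

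Three further inferences are also unsupported. The article does not say that the regression is meant to estimate symptom prevalence, and categorical variables are to be given as frequencies and percentages. The fifth listed assumption is most plausibly loose wording for a collinearity check. And no subsequent trial is described into which errors would be carried.

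**Conclusion.** The method is wrong as written and should be corrected, but the damage is confined to the exploratory longitudinal symptom results. At the record level, independence of errors cannot hold with up to 84 reports per woman.

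For change over time the interval is unreliable in either direction: simulated coverage ran from 99.5% down to 54%, depending on how slopes and serial correlation behave. It would be wrong to say simply that all intervals are too narrow. For overall means or patient-level covariates, if reported, standard errors would be about 3 to 6.5 times too small at an ICC of 0.1 to 0.5, and even an ICC of 0.01 lowers coverage to about 85%.

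The sizes rest on assumed correlations, slope variation and complete diaries, none of which the article supplies. The conclusion that the intervals are invalid needs only some correlation within women.

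**What to change.** In Quantitative Data, replace the multiple linear regression by one of these:

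- a mixed model with a random effect per woman, plus a random time slope if it can be fitted; or
- GEE, or a regression with standard errors clustered by woman.

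A random intercept alone removes the over-wide time interval but not the over-narrow one that arises when slopes differ. If the slope cannot be fitted, the clustered standard errors are the safer choice.

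Remove independence of errors across days within a woman from the list of assumptions, and keep the collinearity check. If the intention is to analyse one summary per woman, say so, since independence is then reasonable. More elaborate specifications are optional; valid intervals do not require them.

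The cost is a sentence or two of text and standard packages in R, which the plan already uses. No new data are needed.

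### Multiple linear regression is the only method named for the daily symptom reports, although up to 84 reports per woman cannot be expected to have independent errors

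*Protocol article*

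**What the plan says.** All references are to the protocol article.

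- **Method.** Quantitative Data, under Statistical Analysis: "The daily self-report of symptoms will be analyzed using multiple linear regression after the variables have been checked by diagnostic plots". The assumptions listed for checking are "1) linearity, (2) homoskedasticity, (3) independence of errors, (4) normality, and (5) independence of independent variables". No other method is named for these data: no random effect, generalised estimating equation, clustered standard error or per-woman summary.
- **Purpose.** The same section says: "The analysis of the obtained data will be based on CIs and will focus on exploring the longitudinal changes over time". The Objective in the abstract includes exploring symptom prevalence and quality of life longitudinally.
- **Data.** The stage 4 assessment table (Table 2) lists "Electronic patient-reported PRO questionnaires on symptoms Bone@BC (everyday") at baseline and in every week to week 12. The abstract's Methods say that participants "will use the app daily for symptom identification and respond to 6 serial patient-reported outcome measurements for 12 weeks".
- **Size.** Power: "Thus, 40-50 participants will be recruited for the intervention". The abstract gives 45 and Table 2 gives 50.
- **Stopping and skipping.** Preestablished Criteria sets a retention criterion ("The retention rate of ≥85% will be the number of individuals who remained in the study") and counts a woman as adherent if she answers at least 80% of the daily questions. The article does not link either rule to the symptom regression.

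**The concern.** Ordinary multiple linear regression treats every row as a separate piece of information. A woman who reports high fatigue on one day is likely to report it the next day, and some women will score higher than others throughout. The errors are therefore correlated within woman by design, and this is known before any data arrive. A diagnostic plot can only confirm it, and the plan does not say what happens then.

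Two things are at stake. First, inference is to rest on confidence intervals, and these would have the wrong width. Second, pooling rows mixes change within women with differences between women. If the women who stop or skip reports are those with worse (or better) symptoms, the mix of women changes over the 12 weeks, and the pooled slope can move although nobody has changed. In a single-arm study no control group would expose this.

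**Working it through.** The plan states no power, alpha or precision figure for this analysis, so there is none to reproduce.

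**Inputs from the article.** Daily reports for 12 weeks: 12 × 7 = 84 per woman at most. Women: 40, 45 or 50, giving 3,360, 3,780 or 4,200 rows at most. A woman at the adherence threshold gives 0.80 × 84 = 67 reports.

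**Assumptions, because the article gives no values.** One row per report; 95% intervals; ICC 0.1 to 0.7; and the slope variation, serial correlation and stopping patterns shown below.

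**Step 1: overall mean or woman-level factor.** The design effect is DE = 1 + (m − 1) × ICC. The ordinary interval is too narrow by a factor of √DE, and its true coverage is 2Φ(1.96/√DE) − 1.

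| ICC | DE, m = 84 | Too narrow by | Coverage | Coverage, m = 67 |
|---|---|---|---|---|
| 0.1 | 1 + 83 × 0.1 = 9.3 | 3.0 | 48% | 52% |
| 0.3 | 25.9 | 5.1 | 30% | 33% |
| 0.5 | 42.5 | 6.5 | 24% | 26% |
| 0.7 | 59.1 | 7.7 | 20% | 22% |

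At ICC 0.5, 3,780 rows carry the information of 3,780/42.5 ≈ 89 independent ones. Simulation (45 women, 84 days, 500 runs per scenario) agrees: coverage for a woman-level covariate was 28% at ICC 0.3 and 21% at ICC 0.5.

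**Step 2: time trend, complete data.** Same simulation, total SD 1 before any slope variation is added, slope expressed over 12 weeks, true mean slope zero.

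| Scenario | Coverage of the ordinary 95% interval |
|---|---|
| Independent rows (check) | 94% |
| Random intercept, ICC 0.3 | 97% |
| Random intercept, ICC 0.5 | 99% |
| ICC 0.5, serial correlation 0.5 | 89% |
| ICC 0.5, slopes varying with SD 0.5 | 80% |
| ICC 0.5, slope SD 0.5, serial correlation 0.3 | 74% |

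In the third row the average reported standard error is 0.055 against a true 0.041 (ratio 1.34, too wide). In the last row it is 0.056 against 0.093 (ratio 0.60, too narrow). The error has no fixed direction.

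**Step 3: time trend with stopping.** ICC 0.5, true slope zero for every woman. Stopping 15% of women is the most that a retention of 85% allows.

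| Stopping | Bias of pooled slope (SD over 12 weeks) | Coverage, ordinary | Coverage, clustered SE | Bias of within-woman slope |
|---|---|---|---|---|
| 15%, random | about 0 | 93% | 97% | 0.00 |
| 15%, moderately related to symptom level | −0.09 | 65% | 81% | 0.00 |
| 15%, strongly related | −0.18 | 11% | 40% | 0.00 |
| 30%, moderately related | −0.16 | 33% | 58% | 0.00 |
| 30%, strongly related | −0.32 | 0% | 4% | 0.00 |

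**Step 4: what repairs what.** Without stopping, standard errors clustered by woman bring coverage back to 92-96% for all three quantities. They do not repair the trend when stopping is related to symptoms, because the estimate itself is biased. Estimating the slope within woman removes that bias when stopping depends on a woman's stable symptom level, which is the only kind of related stopping simulated.

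**The case against.** **Independence is listed as an assumption, and a fallback may be in an analysis plan that is not shown.** It is fair that the plan does not assume independence silently. But the article commits to a named model whose condition the design breaks in advance. That is a poor choice already fixed in the text, not a detail left for later.

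**The unit of analysis is not stated.** This stands as a caveat. One summary per woman would avoid the problem, but the wording about daily self-reports and change over time points to day-level rows.

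**The largest errors concern comparisons that the plan does not name.** This also stands. A reader might infer that symptoms will be compared by education, marital status or drug. The article names no covariates for this regression. Education and marital status appear as examples for the adherence analysis with Fisher's exact test, and no drug comparison is planned. The 3- to 8-fold figure therefore applies to an overall mean, or to a woman-level factor if one is entered. For the stated focus, the time trend, the interval may be too wide or too narrow.

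**The trend need not reflect who is still answering.** A reader might infer that it must. The documents do not support this: nothing in them says that stopping relates to symptoms, random stopping leaves the slope unbiased, and the 85% is a success criterion, not a forecast of dropout.

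**The daily reports are not the only longitudinal symptom data.** A reader might think so, but the QLQ-C30 symptom scales and HADS are also repeated.

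**Little is decided by this analysis.** Correct. The primary outcomes are consent, attrition, retention, technical issues and adherence; acceptability rests on the usability score, interviews and the QLQ-C30. This limits the severity. The fifth listed assumption, on the independent variables, can be read as a collinearity check; it is a wording point that changes no result.

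**Conclusion.** The concern holds, at the level of something that should be fixed in an exploratory analysis. Run on day-level rows, the named method gives intervals of the wrong width:

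- For means and woman-level factors they are too narrow across the whole assumed ICC range, and the result barely changes at 67 reports per woman instead of 84.
- For the time trend the size and direction of the error depend on how much women's slopes vary and how strongly successive days are correlated, neither of which the documents give.
- A spurious trend is possible but conditional on stopping or skipping being related to symptom level. With 15% stopping it was 0.09 to 0.18 SD over 12 weeks under the two patterns of dependence assumed.

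**What to change.** In Quantitative Data, replace multiple linear regression for the daily reports with a linear mixed model that:

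- has a random intercept and a random time slope for each woman;
- allows for serial correlation between days;
- estimates the time effect within woman, separating her stable level from her change.

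For a daily item with a single ordinal response, use the corresponding ordinal mixed model. State that woman is the unit for all standard errors, and say in a sentence how missed and stopped reports are handled. Clustered standard errors or a generalised estimating equation without the within-woman separation would not be enough, as step 4 shows for clustered errors.

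The cost is a paragraph of text, slightly more analysis work in the R software already planned, and wider intervals for means and woman-level factors. No new data are needed, and the feasibility and acceptability criteria in Preestablished Criteria are unaffected.
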